#### Sample size

Sample size selection and estimation was performed based on the CKD diagnosis. Using the GRT sample size calculator,^35^ it is estimated that the intervention will increase diagnosis from the current CKD prevalence of 10% to between 15% and 20%, an increase of 5%–10%. Sample size is estimated based on a 5% increase in diagnosis of CKD. With 80% power, alpha of 0.05 and intraclass correlation coefficient (ICC)=0.05, at least 57 clusters are required per arm. Based on our sampling model, cluster size has been increased to 61 per arm to account for attrition. With an average number of 30 participants per cluster, the total sample size to be targeted is 3660. Based on previous study^11^ that showed a reduction of inappropriate medications in CKD from 32.3% to 17.5% (an approximate reduction of 15%), with 90% power, alpha=0.05 and ICC of 0.05 and a cluster size of 30 per cluster, 19 clusters in each arm are required (38 clusters in all) with a sample size of 1140 for the other primary outcome, that is, change in inappropriate medication use. The sample size required for the diagnosis outcome is, therefore, sufficient to cover the sample size required for the medication changes outcome.

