#### Selection of participants eligible for screening

Participants who are eligible for screening must:

Be between the age of 35 and 74 years.Be at an increased risk of developing CKD due to one or more of the following parameters: ≥60 years of age, hypertension, diabetes, established cardiovascular disease, obesity (body mass index (BMI) ≥30 kg/m^2^), current or former smoker, family history of kidney disease, prior acute kidney injury, Aboriginal & Torres Strait Islander origin.Not have kidney failure or not be receiving kidney replacement therapy.Not have a terminal illness.Not be pregnant.Be able to make independent decisions about their health.

Eligibility will be determined based on self-report by the prospective screening participant and based on the pharmacist’s judgement of the participant being able to make independent decisions about their health.

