#### Secondary outcome measures

Proportion of screening participants with inappropriate medications (number of medications at inappropriate high dose based on the kidney function and number of contraindicated medications).Proportion of eligible participants without potentially beneficial medications (eg, renin angiotensin system inhibitors or sodium glucose co-transporter 2 inhibitors).The number and characteristics of proposed medication adjustments recommended by pharmacists and acceptance rates by GPs.Proportion of participants with CKD risk factors.Proportion of participants screened (process indicator).Participants’ QKidney risk profiles.Percentage of participants referred to their GP.Percentage of participants who take up referral with their GP.Number of hospitalisations due to medication-related events.Cost effectiveness.Health-related quality of life, consumer well-being and satisfaction.

Both the intervention and control group participants will be followed-up by the project officers/pharmacists at 6 and 12 months to determine if they have had any additional blood tests, and changes to their medications, and hospitalisations.

Primary outcomes will be determined based on data collected from GPs. Health-related quality of life and overall participant well-being will be measured using the EuroQoL-5D-5L, which consists of a descriptive system and a Visual Analogue Scale.^39^ The EQ-5D-5L is scored on a 0–1 utility scale, where 0=death and 1=full and complete health. Unit values will be informed by Australian population estimates.^40^ A minimally important difference of 0.07 (7%) change in utility on the EQ-5D-5L scale is considered to be clinically meaningful.^41^

Screening participants’ satisfaction with the service and willingness to pay for the service will be determined by a telephone questionnaire, which will include items relating to service approval (5-point Likert scale); and open-ended questions to elicit reasons for approval and satisfaction ratings. Screening participants’ willingness to pay for the service will also be determined including the maximum amount. Satisfaction of pharmacists (at midtrial and end of trial) with the screening and QUM services will be assessed using electronic surveys. The GPs involved in the care of the participants will also be sent a survey at the end of the trial to determine their satisfaction and any effects on their practice.

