### Data analysis plan

All data will be reported following the Consolidated Standards of Reporting Trial guidelines.^42^ Baseline clinical and demographic characteristics will be summarised using frequencies and percentages for categorical variables, and means, SD, medians, IQRs and minimum and maximum values for continuous variables, as appropriate. All statistical analyses for the primary and secondary outcomes will follow the intention-to-treat (ITT) principle. The ITT population will include all randomised participants based on their initial assignment to either intervention or control group and include any participants who prematurely withdraw or poorly comply with the protocol.

All primary and secondary analyses will use Generalised Estimating Equations with pharmacy as the unit of clustering, using the model appropriate for the distribution of the outcome. The analysis of the primary outcome (reported as a binary variable 0=not diagnosed with CKD, 1=diagnosed with CKD) will use a logistic regression within a model to test the effectiveness of the intervention. Analysis will first be unadjusted (including as fixed factors group membership and the stratification variable, region), followed by analysis adjusted for relevant baseline covariates (age, gender, blood pressure measures, BMI, socioeconomic status and location of pharmacies), as well as the fixed factors from the unadjusted analysis. Binary secondary outcomes such as percentage of participants with CKD risk factors, those having a GP review, and those with potentially inappropriate medications will be analysed using a similar approach as that for the primary outcome.

Additional outcomes including numbers of recommendations made by pharmacists, numbers of medication-related hospitalisations or acceptance rates by GPs will be analysed using negative binomial regression (or Poisson regression, depending on distribution of the outcome) or logistic regression and will include unadjusted and adjusted analyses as per the primary outcome.

For humanistic outcomes such as participant’s health-related quality of life, as well as outcomes on GP satisfaction and participant knowledge/satisfaction, we will use linear regression. All analyses will be presented using unadjusted and adjusted models as per the primary outcome. For the proportion of participants screened in the trial (process indicator), we will use the Mantel-Haenszel extension of a χ^2^ Test of Independence.

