The proportion of missing data will be determined and assessed for any patterns related to the missingness. Unless otherwise stated, multiple imputation (MI) will be used to impute missing values. Missing dichotomous data and categorical data with >2 categories will be assessed using the appropriate MI regression techniques, and missing continuous data will be imputed using chained equations. Sensitivity analyses to explore the effect of imputation will be conducted (eg, complete case; assuming worst case for the missing outcome observations). All tests will be two-sided, with statistical significance set at 0.05 and we will use IBM SPSS Statistics for all analyses unless otherwise specified. There will be no adjustment of the alpha level to account for multiple comparisons because the primary and secondary outcomes are specified, unless otherwise stated to be post hoc.

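### The proportion screened is tested with a Mantel-Haenszel chi-square that ignores clustering, against the plan's own GEE rule; recommendations and GP acceptance have no control-arm counterpart to model

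*Protocol article*

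**What the plan says.** The Data analysis plan gives a general rule: "All primary and secondary analyses will use Generalised Estimating Equations with pharmacy as the unit of clustering". Later in the same section it departs from the rule for one outcome: "For the proportion of participants screened in the trial (process indicator), we will use the Mantel-Haenszel extension" of a chi-square test of independence. No cluster term or cluster adjustment is named. The list under Secondary outcome measures includes this outcome: "Proportion of participants screened (process indicator"). The threshold is general: "All tests will be two-sided, with statistical significance set at 0.05", with no multiplicity adjustment.

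The study design section makes pharmacies the unit of randomisation. It also says that co-located pharmacies within a cluster all receive the same service model.

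The same analysis section assigns count or logistic models to a further group, "Additional outcomes including numbers of recommendations made by pharmacists", medication-related hospitalisations and GP acceptance rates. The unadjusted and adjusted analyses are to follow the primary outcome, whose model has group membership as a fixed factor.

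**The concern.** The two statements on method cannot both hold for the proportion screened. If the specific sentence governs, a listed secondary outcome of a cluster-randomised trial is tested as if participants were independent. Pharmacies are likely to differ on this outcome: the protocol itself plans interviews with high- and low-performing pharmacies, and with high and low recruiters. Ignoring that variation makes the standard error too small, so a difference in reach between arms could be declared when there is none.

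The second issue is estimability. The service that produces medication recommendations to GPs is described for the intervention arm only. A model with arm as a factor then compares an observed count with a structural zero, and an acceptance rate with one that has no denominator.

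**Working it through.** **Inputs.** From Sample size: 10% against 15%, 80% power, two-sided alpha 0.05, ICC 0.05, on average 30 participants per pharmacy, 57 clusters per arm raised to 61. From the study design section: 1:1 allocation and 38/12, 30/10 and 20/12 metropolitan/rural pharmacies in the three states. The ICC and cluster size were set for CKD diagnosis and reused for inappropriate medication. Applying them to the proportion screened is an assumption.

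**The plan's own figure.** The protocol states: "With 80% power, alpha of 0.05 and intraclass correlation coefficient (ICC)=0.05, at least 57 clusters are required per arm".
- Individually randomised size per arm, with pooled variance under the null: [1.96·√(2 × 0.125 × 0.875) + 0.8416·√(0.10 × 0.90 + 0.15 × 0.85)]² / 0.05² = 686 after rounding up.
- Design effect: 1 + (30 − 1) × 0.05 = 2.45.
- Clusters per arm: 686 × 2.45 / 30 = 56.02, rounded up to 57.
- Total: 61 × 2 × 30 = 3660.

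The stated figures reproduce, so this is how the plan itself allows for clustering.

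**Type I error when clustering is ignored.** The true variance is the design effect (DE) times the assumed one, so the actual two-sided error is 2 × [1 − Φ(1.96/√DE)]. At ICC 0.05 and m = 30, 1.96/√2.45 = 1.252, which gives 21.05%.

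| ICC | m | DE | Actual error of a nominal 5% test |
|---|---|---|---|
| 0.01 | 30 | 1.29 | 8.4% |
| 0.02 | 30 | 1.58 | 11.9% |
| 0.05 | 30 | 2.45 | 21.1% |
| 0.10 | 30 | 3.90 | 32.1% |
| 0.05 | 10 | 1.45 | 10.4% |
| 0.05 | 20 | 1.95 | 16.1% |
| 0.05 | 60 | 3.95 | 32.4% |
| 0.05 | 100 | 5.95 | 42.2% |

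**Can stratification rescue the test?** Arm does not vary within a pharmacy, so strata formed by pharmacy contain no comparison. Strata formed by region leave the between-pharmacy variation in place. This was simulated with beta-binomial data under no effect, a Mantel-Haenszel test stratified by state and metropolitan/rural (19, 6, 15, 5, 10 and 6 pharmacies per arm), m = 30 and 20,000 runs per setting. At ICC 0.05 the rejection rate was 21.0% to 21.3% for true proportions of 0.1, 0.5 and 0.8. A cluster-level t-test with the same strata, standing in for the plan's GEE, rejected in 5.1% to 5.2% of runs.

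**Recommendations and acceptance.** No arithmetic applies; the sections are set side by side.
- The abstract attaches the QUM service to the intervention group only.
- Selection of pharmacists: the fourth training module is the QUM service, and control pharmacists take modules 1 to 3.
- Clinical protocol and recruitment procedure: control participants receive risk assessment, advice, counselling and fact sheets. Medication recommendations to the GP are described only for the intervention group.
- Data analysis plan: recommendations and acceptance are modelled in the manner of the primary outcome, with group as a factor.

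The control count of recommendations is therefore zero by design, and control acceptance has no denominator. Medication-related hospitalisations, covered by the same sentence, can occur in both arms and can be compared.

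**The case against.** The strongest objection is that 21% is borrowed. The 30 per pharmacy is a recruitment target for enrolled participants. A proportion screened needs a denominator of people approached, eligible or enrolled, and the article does not say which. That stands: 21% is an illustration, and a reader who takes it as the trial's actual error rate for this outcome goes beyond the document. The direction does not depend on it, since every value in the table exceeds 5%.

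A second objection is that the hypotheses do not mention the proportion screened, and that both primary outcomes and the other binary secondary outcomes keep the clustered GEE. That also stands and limits the importance. A third is that the sentence on recommendations and acceptance is condensed and also covers hospitalisations, where an arm comparison is valid; an empty control cell would be noticed at once. That is fair, so this part is a correction of wording rather than a route to a false conclusion.

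A reader might also infer that the outcome on CKD risk factors cannot be tested. The plan lists "Binary secondary outcomes such as percentage of participants with CKD risk factors" for a logistic model, while eligibility demands that a participant "Be at an increased risk of developing CKD due to one or more of the following parameters". The documents support this only for having any factor at entry, which is 100% in both arms. Table 1 schedules the measure again at 6 and 12 months, and single factors such as obesity or hypertension can change. A comparison of individual or modifiable factors at follow-up is therefore meaningful; the outcome needs defining, not removing.

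**Conclusion.** The concern holds for the process indicator. The named test contradicts the general GEE rule in the same section and is anti-conservative in a trial that randomises pharmacies. The size is conditional: about 21% type I error if the ICC of 0.05 and 30 per pharmacy are carried over, 8% to 32% for ICC 0.01 to 0.10 at 30 per pharmacy, and 10% to 42% for 10 to 100 per pharmacy at ICC 0.05. These figures assume equal pharmacy sizes and no true difference.

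It also holds for recommendations and GP acceptance, on the reading that modelling them like the primary outcome includes the arm factor: that effect is not estimable. Neither part touches the primary analyses. The plan should be corrected on both, but the trial's main conclusions do not depend on it.

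**What to change.** 1. Delete the Mantel-Haenszel sentence and analyse the proportion screened with the plan's pharmacy-clustered logistic GEE, stating the denominator. If only aggregate counts exist for people not screened, compare pharmacy-level proportions between arms instead.
2. Report numbers of recommendations and GP acceptance rates in the intervention arm only, with cluster-robust intervals. Keep the between-arm model for medication-related hospitalisations.
3. State that any between-arm comparison of CKD risk factors concerns individual or modifiable factors at 6 and 12 months, since having any factor is 100% at entry. Keep the assessments scheduled in Table 1.

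The cost is a few lines of wording. The p value for the process indicator will be less extreme, and a formal between-arm test is given up for two outcomes where none was possible.

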**Methods and analysis:**

This study is a multicentre, pragmatic, two-level cluster randomised controlled trial which will be conducted across different regions in Australia. Clusters of community pharmacies from geographical groups of co-located postcodes will be randomised. The project will be conducted in 122 community pharmacies distributed across metropolitan and rural areas. The trial consists of two arms: (1) Control Group: a risk assessment using the QKidney CKD risk assessment tool, and (2) Intervention Group: a risk assessment using the QKidney CKD plus Point-of-Care Testing for kidney function markers (serum creatinine and estimated glomerular filtration rate), followed by a QUM service. The primary outcomes of the study are the proportion of patients newly diagnosed with CKD at the end of the study period (12 months); and rates of changes in the number of medications considered problematic in kidney disease (number of medications prescribed at inappropriate doses based on kidney function and/or number of nephrotoxic medications) over the same period. Secondary outcomes include proportion of people on potentially inappropriate medications, types of recommendations provided by the pharmacist (and acceptance rate by general practitioners), proportion of people who were screened, referred, and took up the referral to visit their general practitioners, and economic and other patient-centred outcomes.

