### Hypotheses

We hypothesise that the use of a POCT with CKD risk assessment (POCT+QKidney Risk Assessment: Intervention Group) in community pharmacies will result in (1) a significantly improved detection of previously unknown CKD cases, and (2) reduced use of potentially inappropriate medications when compared with CKD risk assessment alone (QKidney Risk Assessment: Control Group).

Other hypotheses related to the primary hypothesis are that the Intervention Group will be associated with a statistically significant increase in the proportions of those who are referred to the GP, take up referral with the GP, are newly diagnosed with CKD compared with the Control Group.

Additionally, the incorporation of POCT in conjunction with the QKidney Risk Assessment will lead to enhanced utilisation of kidney beneficial medications (ie, those that slow kidney disease progression), a long-term economic benefit and improved humanistic outcomes.

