### Outcomes

#### Primary outcome measures

Proportion of patients newly diagnosed with CKD at the end of the study period.Changes in the number of medications considered problematic in kidney disease (number of medications prescribed at inappropriately high dose, number of contraindicated medications or detrimental drug interactions).

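### Two primary outcomes are each tested at two-sided 0.05 with no adjustment because they are pre-specified, which does not control the error across the two tests

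*Protocol article*

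**What the plan says.** The abstract refers to primary outcomes in the plural ("The primary outcomes of the study are the proportion of patients newly diagnosed with CKD", followed by the medication outcome), and the Primary outcome measures section lists the same two. The Sample size section sizes diagnosis first ("Sample size is estimated based on a 5% increase in diagnosis of CKD": 80% power, alpha 0.05, ICC 0.05, 57 clusters per arm, raised to 61 for attrition). It then gives a separate calculation "for the other primary outcome, that is, change in inappropriate medication use" (90% power, alpha 0.05, 19 clusters per arm).

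The Data analysis plan states "All tests will be two-sided, with statistical significance set at 0.05" and then "There will be no adjustment of the alpha level to account for multiple comparisons because the primary and secondary outcomes are specified". The sentence ends with an exception for comparisons stated to be post hoc. The Hypotheses section expects "1) a significantly improved detection of previously unknown CKD cases, and (2) reduced use of potentially inappropriate medications". No section gives a testing order, a split of alpha, or a rule that both outcomes must be significant.

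**The concern.** The plan takes an explicit decision and gives one reason for it, so this is not a detail left to an analysis plan that is not shown. The reason does not support the decision. Pre-specification guards against selecting outcomes after seeing the data. Two pre-specified tests at 0.05 still give two chances of a false positive.

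With no rule linking the outcomes, the protocol leaves open that significance on either one alone is reported as success on a primary outcome. In that case the chance of a false primary finding is close to double that of a single test. A split result, with one outcome significant and the other not, would also have no pre-agreed reading.

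**Working it through.** **Inputs.** From Sample size: diagnosis 10% against 15%; medication 32.3% against 17.5%; ICC 0.05; 30 participants per cluster; 57 clusters per arm required and 61 targeted. From Data analysis plan: two-sided 0.05 per test. The documents give no correlation between the two test statistics, so the correlations below are assumptions.

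**The plan's own figure.** The pooled two-proportion formula is n = [z(1−α/2)·√(2p̄(1−p̄)) + z(power)·√(p₁(1−p₁)+p₂(1−p₂))]² / (p₁−p₂)².
- With p̄ = 0.125: (1.960×0.4677 + 0.842×0.4664)² / 0.05² = 686 per arm.
- Design effect: 1 + 29×0.05 = 2.45.
- Clusters: 686×2.45/30 = 56.02, rounded up to 57 per arm. This reproduces the plan, so the diagnosis outcome uses the full two-sided 0.05.
- The medication figure of 19 does not reproduce in this way (178×2.45/30 = 14.5, so 15). The stated number is larger, and the difference does not affect this point.

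**Error across the two primary tests, both nulls true.**
- Independent tests: 1 − 0.95² = 0.0975. The upper bound is 0.05 + 0.05 = 0.10.
- Bivariate normal test statistics:

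| Assumed correlation | At least one false positive, either direction | At least one false positive favouring the intervention |
|---|---|---|
| 0 | 9.75% | 4.9% |
| 0.3 | 9.5% | 4.8% |
| 0.5 | 9.1% | 4.5% |
| 0.7 | 8.3% | 4.2% |
| 0.9 | 7.0% | 3.5% |

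At correlation 0 the last column is 1 − 0.975² = 4.9%. A single two-sided 0.05 test gives 5% and 2.5% respectively.

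**Power under possible repairs.** The effective number per arm for diagnosis at 61 clusters is 61×30/2.45 = 747.
- Diagnosis at 0.05: 83.3%. At 0.025: 75.2%.
- At 57 clusters (57×30/2.45 = 698): 80.7% and 72.1%.
- Medication at 0.025 with 61 clusters: above 99.9% if all 30 per cluster contribute. This treats the outcome as a proportion, as the Sample size section does.
- Holm, independent tests: diagnosis power = 0.752 + (0.833 − 0.752) × (medication power at 0.025). With medication power near 1 this is 83%.
- Suppose only 3 per cluster contribute to the medication outcome (an assumption). The effective number is 61×3/(1+2×0.05) = 166 per arm, medication power at 0.025 is 81%, and diagnosis power under Holm is 0.752 + 0.080×0.81 = 82%.
- If the medication outcome is null: 0.752 + 0.080×0.025 = 75%.
- Fixed order with diagnosis first: diagnosis 83%; medication 0.833 × (above 0.999) = about 83%. Under Holm, medication power stays above 99%.

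**The case against.** The strongest reply is that the two outcomes answer different questions. Trial objectives gives separate aims for screening and for the medicines service, and Hypotheses numbers them separately. If each claim rests only on its own test, 0.05 per hypothesis is a defensible and debated choice. The plan's 0.05 is indeed a per-test level; no trial-wide level is stated, so the plan cannot be said to breach one. That part of the reply stands. But the plan does not argue that the claims are separate. Its only reason is that the outcomes are specified, and it does not say how a split result would be reported.

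A second reply is that the hypotheses are joined by the word and, so both must succeed. That would remove the need for adjustment, but it is nowhere stated as a decision rule, and each outcome is powered alone.

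A reader might infer three stronger points that the documents do not support:
- **A chance of nearly 10% of falsely declaring benefit.** The 9.75% counts errors in both directions. For claims favouring the intervention the figure is 4.9%, and both figures fall as correlation rises.
- **Further inflation from choosing between the unadjusted and adjusted models.** The Data analysis plan gives the order in which they are run. Which one is confirmatory is commonly settled in an analysis plan, and that is not shown.
- **Testing diagnosis first as the cheapest repair.** On the plan's assumptions it lowers medication power to about 83%, while Holm keeps it above 99% with the same diagnosis power.

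**Conclusion.** The point holds in a limited form. Pre-specification is not a reason to leave two primary tests unadjusted, and no rule in the protocol makes adjustment unnecessary. The chance of at least one false-positive primary test is 9.75% if the tests are independent, and 9.5% to 9.1% at assumed correlations of 0.3 to 0.5. For false claims of benefit it is 4.9% against 2.5%. These figures assume that both nulls are true and that either result alone can support a primary claim. The protocol does not exclude that reading, but does not state it either. The data would remain usable. What needs settling before outcomes are analysed is the rule for making a primary claim.

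**What to change.** In the Data analysis plan, replace the no-adjustment sentence, for the two primary outcomes only, with the Holm procedure: compare the smaller p-value with 0.025 and, if it passes, the other with 0.05. This holds the error across the pair at 5% or less whatever their correlation. Leave secondary outcomes unadjusted and say so.

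The text change is one paragraph, with no change to the number of clusters. Diagnosis power at 61 clusters per arm stays at about 83% if the medication effect is as planned, and at about 82% even under the 3-per-cluster assumption. The real cost arises if the medication outcome is null. Diagnosis is then in effect tested at 0.025, and its power falls from 83% to about 75% at 61 clusters, or from 81% to 72% at 57.

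If the sponsor intends that both outcomes must be significant, stating that rule is an adequate alternative and needs no adjustment. The price is that no primary claim could then rest on one outcome alone.
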